#### Intervention, DE-HBWC arm

The DE-HBWC program was devised through three phases of crafting the research questions, EBP, identifying the barriers and facilitators to intervention implementation, and, ultimately, through meetings with experts and pre-experiments. The DE-HBWC program is a personalized one-on-one treatment program for chronic wound patients delivered by specialist wound nurses using a combination of online and offline intervention modes. Conducting remote video visits through electronic facilities weekly to evaluate wounds and provide guidance on dressing changes online, and offline home medication change, assessment, and health guidance services are provided by wound specialist nurses every 2 weeks. During weekly remote assessments, all aspects of wound care are carefully assessed by a wound specialist nurse and documented with the assistance of a graduate nursing student. This includes wound morphology, which encompasses tissue type, dimensions, and color profiles, as well as exudate metrics such as volume, consistency, and the presence and severity of odor. The assessment also evaluates the periwound status, focusing on skin integrity, sinus tract characteristics, and signs of infection. Furthermore, pharmacological interventions are thoroughly recorded, including antimicrobial therapies and adjunctive agents, along with detailed application protocols. Lastly, the documentation tool supports intervention tracking by capturing dressing protocols, debridement frequency, and the provision of health education to patients and caregivers.

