The program is overseen by a wound care specialist physician who is responsible for reviewing patient progress biweekly through electronic records. This physician also approves any necessary adjustments to treatment plans. Nursing graduate students are responsible for assisting with text recording and data organization. Additionally, nurses play a pivotal role in coordinating care with primary care providers utilizing the hospital’s integrated electronic health record system, ensuring seamless communication and continuity of care. The Deputy Director of Nursing is responsible for overseeing the project implementation and ensuring quality control. Patients are provided with access to a telehealth hotline designed to address urgent concerns, such as sudden onset of pain, fever, or purulent drainage. This resource ensures that patients can promptly seek assistance for complications that may arise during their treatment. The escalation protocol ensures tiered clinical responses: (1) patients with suspected wound deterioration (e.g., increased erythema, purulent drainage, or systemic symptoms) initiate real-time telehealth consultations with certified wound specialist nurses; (2) nurses triage cases to physicians for urgent directives, prioritizing same-day in-person evaluations for high-risk scenarios; and (3) physicians determine hospitalization needs based on standardized severity criteria (e.g., sepsis risk, necrotizing infection).

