#### Control, TH arm

Participants in the control group underwent offline traditional treatment at the Wound Treatment Clinic of Fujian Provincial Hospital, and the intervention cycle and dressing change principles were the same as those for the intervention group. Patients in the control group attended the Wound Treatment Clinic every other day for dressing change, assessment, and health guidance. The frequency of dressing changes is flexibly adjusted by the wound specialist nurses according to the patient’s patient wound healing status. Wound specialist nurses delivered the interventions, while nursing graduate students collected patient data using the hospital’ s in-house chronic disease management platform.

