### Study outcome measures

The primary outcome measures are wound healing based on the commonly used Bates-Jensen Wound Assessment Tool (BWAT) (28) and the Wound treatment table, which was formulated by our team, based on previous research (29), to evaluate the size, depth, and exudation of chronic wounds; drugs; dressings used for treatment; cost; healing duration; as well as the round-trip transportation and waiting time. Wound images will be acquired weekly and recorded and analyzed using Three Dimensions (3D) AI reconstruction technology. Empirical evidence demonstrates that 3D wound measurement devices achieve comparable accuracy to traditional nurse-performed measurements using manual scales (*p* > 0.05), while significantly reducing procedural time (*p* < 0.05) (30). Caregivers or patients can upload wound photographs through a smartphone application. The AI system automatically generates a 3D model of the wound and identifies areas that require attention, such as those with a “high infection risk.” This tool is particularly beneficial for rural or homebound patients, as it enables specialists to conduct remote assessments of wounds, thereby minimizing the necessity for in-person visits. The secondary outcome measures included participants’ quality of life, health status, wound self-management, satisfaction, and cost-effectiveness. The Chronic Wound Patient Quality of Life Scale (Wound-QoL) (31), Chronic Wound Self-Management Scale (32), and the 36-Item Short Form Survey (SF-36) (33) will be used to evaluate health, quality of life, and wound self-management. Satisfaction survey forms will be used to measure patient satisfaction with wound care. The economic benefits of intervention measures will be evaluated by measuring the cost–benefit and incremental cost–benefit ratio of wound care for the two groups of participants. More information about the sensitivity and specificity of the assessment methods can be found from the reference 28, 29.

All outcome measures and assessment time points are shown in Table 2.

**Table 2 tab2:** Assessment outline and timelines.

Measures/time point	Pre-intervention	Intervention period	Post-intervention	Follow-up
	0 weeks		12-week	24-week
Eligibility assessment				
Inclusion criteria	×			
Exclusion criteria	×			
Informed consent	×			
Allocation	×			
Intervention				
DE-HBWC group				
Traditional hospital treatment control group				
Demographics and other baseline characteristics	×			
Primary outcomes				

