## Discussion

This study aimed to evaluate the impact of the DE-HBWC program on wound healing and quality of life in chronic wound patients and to assess its economic benefits. Although DE-HBWC programs have been used in the treatment of chronic wounds and have achieved promising results, some implementation-related problems persist (18, 35). This study is a new exploration of the implementation of a DE-HBWC program based on a scientific framework employed in implementation research, namely, the five-step PEDALs model research paradigm. Barriers to the implementation of the DE-HBWC project as well as facilitators were identified through qualitative interviews. The intervention program was formulated based on the results of the literature research and qualitative interviews, and the program was modified and improved through expert meetings and small sample pre-testing to ensure a more rigorous, scientific, operable, and feasible program development process.

The present DE-HBWC program potentially represents a convenient and low-cost wound care model for chronic wound patients, enabling them enjoy hospital-level care in a home setting. It solves the problem of the inconvenience caused to patients in leaving their homes, having to undertake journeys to hospital, and waiting to receive in-person medical care, and if therefore especially beneficial for patients with mobility problems such as those who are disabled or older adults. In addition, a rigorous methodological design will be used to reduce bias, including randomization, blinding, use of a control group, recruitment strategies, rigorous eligibility screening, and pilot trials. Potential selection bias in the control and intervention groups will be minimized by the above strategies.

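### The outcome list that the article declares complete has no harm outcome, and no between-arm comparison of harms is planned, although the home arm has far fewer scheduled in-person nurse contacts

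*Protocol article*

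**What the plan says.** The section *Study outcome measures* closes the list itself: "All outcome measures and assessment time points are shown in Table 2". The primary outcome is healing: "The primary outcome measures are wound healing based on the commonly used Bates-Jensen Wound Assessment Tool (BWAT"), together with a team-made wound treatment table and 3D image analysis. For the rest, "The secondary outcome measures included participants’ quality of life, health status, wound self-management, satisfaction, and cost-effectiveness". Table 2 repeats these items and adds nothing on safety.

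The two arms differ in how often a nurse sees the wound in person. Control patients "attended the Wound Treatment Clinic every other day for dressing change, assessment, and health guidance". In the home arm, "offline home medication change, assessment, and health guidance services are provided by wound specialist nurses every 2 weeks", alongside weekly video assessment. Visit frequency in the home arm and dressing-change frequency in the control arm may both be adjusted.

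The home arm also has a 24-hour hotline, recording of infection signs at the weekly remote assessment, and an escalation route whose last step reads "physicians determine hospitalization needs based on standardized severity criteria (e.g., sepsis risk, necrotizing infection"). The section *Control, TH arm* describes no counterpart.

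Adverse events appear in *Criteria for discontinuing or modifying allocated interventions*, as a reason to end participation and as something to follow up in the individual. That section also says that data on participants who stop the trial are collected only up to the point of exit. *Data collection and statistical analysis* covers models, subgroups and imputation, but no harm comparison.

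**The concern.** With fewer in-person assessments, the obvious clinical risk is that deterioration is recognised late. The document foresees this, since it builds a hotline and an escalation route for suspected deterioration. Its introduction also names infection and amputation among the complications that make chronic wounds a burden, and cites lower infection risk as a benefit of digital care. The harms are known to the authors, but they are not among the outcomes.

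The conclusions in view are broad. The discussion describes the program as "enabling them enjoy hospital-level care in a home setting", and *Phase V: Long-term* plans institutional adoption and insurance coverage. As written, the trial could report faster healing, lower cost and better satisfaction, and move to scale-up, with no table showing infections or admissions by arm.

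The gap is hard to repair later. If harms are assembled afterwards from whatever each care pathway happened to record, the arms will have been observed through different channels, and no analysis can restore equal ascertainment.

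**Working it through.** **1. The list against the harms.**

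| Item | In Table 2? | Elsewhere in the article |
|---|---|---|
| Healing (BWAT, wound treatment table, 3D image) | Yes; biweekly or weekly, then weeks 12 and 24 | Size, depth, exudation, drugs, dressings, cost, healing duration |
| Wound-QoL, self-management, SF-36 | Yes; weeks 0, 12, 24 | – |
| Cost-effectiveness, satisfaction | Yes; week 12 | – |
| Wound infection | No | Signs recorded at the remote assessment, home arm only |
| Hospital admission | No | Last step of the escalation route, home arm only |
| Amputation | No | Introduction, as a complication |
| Death | No | Not mentioned |
| Adverse events | No | Stopping reason and individual follow-up |

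**2. Size of the contact contrast.** Inputs: a 12-week intervention (84 days); clinic every other day; home visit every 2 weeks; video weekly.

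- Control, in person: 84 / 2 = 42.
- Home arm, in person: 12 / 2 = 6. Ratio 42 / 6 = 7.
- Home arm with video: 6 + 12 = 18. Ratio 42 / 18 ≈ 2.3.

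These are nominal counts for the full 12 weeks without frequency adjustment, and they treat video and home visits as separate contacts. The ratios do not depend on duration: each fortnight has 7 clinic visits against 1 home visit, or against 3 contacts with video.

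**3. The plan's own sample size.** Inputs from *Sample*: means 38.64 and 32.54, SD 8.21, alpha 5% (two-sided, from the analysis section), power 90%.

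- Difference: 38.64 − 32.54 = 6.10.
- Normal approximation: n = 2(1.960 + 1.282)² × 8.21² / 6.10² ≈ 38.1, so 39 per arm.
- Two-sample t-test: 39.05, so 40 per arm (power 0.907 at 40).
- Dropout: 40 / (1 − 0.20) = 50 per arm, 100 in total.

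The stated figure reproduces. It was set for healing time, so the next question is what it offers for harms.

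**4. What 50 per arm can say about harms.** The document gives no infection or admission rate, so the rates below are assumptions.

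- Zero events in 50: upper one-sided 95% bound ≈ 3 / 50 = 6%.
- Half-width of the 95% interval for a risk difference, with the same rate p in both arms: 1.96 × √(2p(1 − p)/50).

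| Assumed rate p | Half-width, 50 per arm | Half-width, 40 per arm |
|---|---|---|
| 5% | 8.5 points | 9.6 points |
| 10% | 11.8 points | 13.1 points |
| 20% | 15.7 points | 17.5 points |

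| Assumed rates | Power, 50 per arm | Per arm for 80% power |
|---|---|---|
| 5% vs 10% | 0.16 | 435 |
| 5% vs 15% | 0.38 | 141 |
| 10% vs 20% | 0.29 | 199 |
| 10% vs 30% | 0.71 | 62 |
| 20% vs 40% | 0.59 | 82 |

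A harm comparison here is an estimate with an interval. Even a doubling from 10% to 20% would usually not reach significance.

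**The case against.** **A condensed article may leave safety reporting to the full protocol or analysis plan.** This is the strongest reply. Adverse events are not ignored: for a participant who withdraws because of a related event, it is followed until resolved or stable, and unrelated events are followed to the end of the trial. One could read Table 2 as listing effectiveness outcomes only. What stands is that methods of tabulation may well sit elsewhere. But the sentence in question covers all outcome measures without qualification, and what is measured, when, and in which arm has to be fixed before data collection.

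**The healing instruments would register deterioration.** Partly right. A reader might infer that escalated cases enter no outcome at all, and the document does not support that. An infected wound would be expected to affect exudation, size, drug use, cost and healing duration, all recorded in both arms. The narrower point survives: infection, admission, amputation and death are not defined or compared as events.

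**The home arm is not left with one visit a fortnight.** Correct. Weekly video, image-based prioritisation, adjustable visits, the hotline and biweekly physician review all count as mitigation. The 7-fold ratio holds only for in-person contact. Mitigation does not measure harm, however.

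**The direction of any ascertainment imbalance is unknown.** Also correct. The home arm has a hotline and an escalation route, but control patients are seen in person every other day. The document describes no hotline or escalation log, so it gives no basis for saying which arm would be over-counted. The channels differ, and that is enough to call for one common method.

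**The trial is too small for safety.** True for a test. It is an argument for intervals and restrained wording, not for leaving harms out.

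**Conclusion.** The concern holds. A list declared complete contains no harm outcome and no comparison of harms between arms is planned, in a trial whose contrast is about 42 against 6 scheduled in-person contacts, or 42 against 18 with video. The counts assume 12 full weeks at the nominal frequencies.

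Two stronger readings should be resisted. Nothing here shows that home care is less safe; the plan simply would not compare it. Nor is the trial set up to demonstrate equivalence with hospital care. The idea of equal treatment is background in the abstract, the stated aims are healing, quality of life and economic benefit, and the sample size targets a difference in healing time. The issue is what a favourable result could be used to support.

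The rule ending data collection at exit adds to the gap: harms that first arise after a participant leaves the trial would not be captured. The point should be addressed but does not undermine the primary comparison. The precision figures rest on assumed event rates of 5% to 20%.

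**What to change.** Add a safety row to Table 2 for both arms: wound infection (one definition for both), unplanned hospital admission, amputation and death. Ascertain these identically, from the hospital record plus one standard question at the existing biweekly, week-12 and week-24 assessments. Do not rely on information that only one arm's pathway generates. Continue ascertainment after the allocated intervention is discontinued, where consent allows, and align the rule on data collection after exit with this.

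In the analysis section, state that events will be reported by randomised arm as risk differences with 95% confidence intervals, described as estimation and not as a powered test. State also that the report will not claim that home care is as safe as clinic care beyond what those intervals support.

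The cost is one table row, one question, a record check and one descriptive table. No change to care in either arm is needed. The drawback is wide intervals, which must be reported as such.

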### Data collection and statistical analysis

Enrolled subjects will be scheduled to complete the baseline data collection. Data will also be collected after 12 and 24 weeks for outcomes, and data on the primary outcome, wound healing, will be collected biweekly. All data analysis will be performed using SPSS Statistics v21.0 (IBM). A two-tailed approach will be used, with *α* level set to 0.05 for testing. To ensure that outcome evaluators and data analysts are not influenced by group assignment, they will not interact with participants, except in the case of outcome evaluators during data collection. Descriptive statistics will be used to summarize demographic and other baseline characteristics. Tests of normality of data distribution were validated using Kolmogorov–Smirnov. After approaching normality for each variable, two-sample independent *t*-tests, x^2^-tests (or Fisher’s exact tests), or nonparametric tests, as appropriate, were used to compare normally distributed variables between the intervention and control groups. If necessary, the results will be adjusted based on potential confounding factors such as age, gender, and education level. Statistical analysis will be based on the intention-to-treat (ITT) method (34).

Generalized linear mixed effects models (GLMM) will be used to estimate the odds ratio (OR) and 95% confidence intervals (CIs) for assessing whether changes in outcome indicators are significantly different over time. Models include randomized groups with time as a fixed effect and time × group as an interaction effect to account for the correlation between repeated observations for each participant. Characteristics such as patient age, gender, wound type, and wound size will be adjusted for as covariates. In addition, to explore the effect of baseline characteristics on intervention effect sizes, we will conduct subgroup analyses by testing for interactions between subgroups and intervention effects. Predefined subgroup analyses will be conducted for baseline characteristics including age, gender, education, monthly income, wound type, and wound size. The main outcomes of the subgroup analyses are *p*-values for the group × time × characteristics interaction coefficients and estimates (95% CIs) of the differences between the intervention and control groups within each subgroup. Finally, sensitivity analyses will be performed by interpolating missing data using a random forest model to improve the reliability of our findings.

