### Sample

The recruitment and screening of all participants were conducted on the online platform of Fujian Provincial Hospital’s WeChat official account or the hospital’s offline wound treatment clinic. This is a randomized controlled trial consisting of two branches and three evaluation stages (T0, baseline; T1, 12-week post intervention; T2, 24-week follow-up). The intervention-group participants received DE-HBWC project wound treatment at their own homes, while the control group participants received treatment at traditional hospital wound-treatment clinics. The required sample size was estimated using PASS v15.0 (NCSS, LLC, United States), based on a completely random design, to compare the mean values of two independent samples. Based on our previous wound treatment results for the healing time of chronic wounds and using two-sample T-tests assuming equal variance procedure of PASS v15.0, μ1 = 38.64, μ2 = 32.54, *σ* take 8.21, a sample size of 40 participants per group was determined to be sufficient to detect an effect with a type 1 error rate of 5 and 90% power. Assuming a drop-out rate of 20%, a total of 100 participants will be needed, with 50 participants in each group.

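### A Kolmogorov–Smirnov check appears to choose between a t-test and an unnamed rank test, so a p-value for cost may not test the mean costs on which the incremental cost ratio rests

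*Protocol article*

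**What the plan says.** All references are to the protocol article.

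- **Data collection and statistical analysis**, on normality: "Tests of normality of data distribution were validated using Kolmogorov" (the Kolmogorov–Smirnov test). No threshold is given, and the text does not say whether the test is run per arm or on pooled data, or in which version.
- **Same section**, on comparing arms: after t-tests and chi-square or Fisher tests, the sentence ends "nonparametric tests, as appropriate, were used to compare normally distributed variables between the intervention and control groups". No rank test is named and no test is tied to an outcome. On sidedness: "A two-tailed approach will be used", at 0.05.
- **Same section, next paragraph**: a generalized linear mixed model (GLMM) with group, time and their interaction, reported as odds ratios, for change in the outcomes over time.
- **Study outcome measures**: the team's wound treatment table, listed under the primary outcomes, also records "drugs; dressings used for treatment; cost; healing duration; as well as the round-trip transportation and waiting time". Incremental cost ratios are a secondary outcome. Table 2 places the economic outcome at 12 weeks only.
- **Sample**: the calculation is "Based on our previous wound treatment results for the healing time of chronic wounds", made "to compare the mean values of two independent samples", with "μ1 = 38.64, μ2 = 32.54, *σ* take 8.21".

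**The concern.** A t-test compares means and a rank test compares rank order. If a significance test on the trial's own data picks between them, the quantity compared is not fixed in advance. The sentence also misfires as written: it applies nonparametric tests to normal variables and leaves no stated rule for the others.

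This matters most for cost. An incremental cost ratio has a difference in mean cost in its numerator, and costs and waiting times are often skewed. The arms may also differ in spread as well as level. Controls attend the clinic every other day, subject to adjustment, whereas intervention patients have weekly video visits and home visits every two weeks, without on-site service fees. In that situation a rank test can report a cost difference when mean costs are equal, or miss one carried by a few expensive patients. The report could then give a cost p-value that points away from its own ICER.

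**Working it through.** **1. The plan's own figure.** The difference is 38.64 − 32.54 = 6.10, with SD 8.21, two-sided 5% and 90% power. By the normal approximation, n = 2(1.960 + 1.282)² × 8.21² / 6.10² ≈ 38.1, so 39 per group. The exact t-test solution is 39.05, so 40 per group (power 0.907). Then 40 / 0.80 = 50 per group and 100 in total. The stated size reproduces.

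**2. Effect of a switch on healing time.** If healing time is normal, Mann–Whitney has relative efficiency 3/π = 0.955. It needs 39.05 / 0.955 = 40.9, so 41 per group, and has power 0.893 at 40 against 0.907. N is in effect untouched. A normal healing time would still fail a correctly calibrated 5% check in at least one arm in about 1 − 0.95² ≈ 10% of trials.

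**3. Why ranks and means part.** Assume lognormal costs with mean 1 in both arms. The log-variance is ln(1 + CV²) and the median is 1/√(1 + CV²).
- CV 0.5 vs 1.0: log-variances 0.223 and 0.693; medians 0.894 and 0.707. The chance that a patient in the first arm costs more than one in the second is Φ[(0.693 − 0.223)/2 ÷ √(0.223 + 0.693)] = Φ(0.245) ≈ 0.60.
- CV 0.5 vs 0.75: log-variances 0.223 and 0.446; Φ(0.136) ≈ 0.55.

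A rank test responds to this departure from 0.50 although mean costs are equal.

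**4. Size of the effect.** Simulated trials, equal lognormal means. Kolmogorov–Smirnov is applied at 5% in each arm with estimated mean and SD; if either arm rejects, Mann–Whitney is used, otherwise the t-test. Figures are the share of trials reporting a difference, rounded.

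| n per arm | CVs | Two-stage rule | Welch |
|---|---|---|---|
| 50 | identical | 5% | 5% |
| 50 | 0.5 vs 0.75 | 11% | 5% |
| 50 | 0.5 vs 1.0 | 32% | 7% |
| 40 | 0.5 vs 1.0 | 23% | 7% |

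With the Lilliefors correction, the CV 0.5 vs 1.0 results rise to about 42% at 50 per arm (39–42% across runs) and 32% at 40. The version matters because, at 50 per arm and these CVs, the uncorrected check flags 63% of trials and the corrected one 99%.

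**5. Source of the excess.** Mann–Whitney alone, with no pre-test, rejects in about 42% of trials at 50 per arm and CV 0.5 vs 1.0. The excess therefore comes from the rank test not comparing means.

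**6. The opposite error.** With 40 per arm, equal medians and a mean ratio of 1.45 (log-SD 0.5 vs 1.0), Mann–Whitney rejects in 6% of trials and Welch in 25%.

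**The case against.** A normality check before choosing between a t-test and a rank test is common practice, and an article may leave the method for each variable to a fuller document. That would answer a silence. Here the article states a selection rule, and states it in a form that cannot be applied as written.

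Several points on the other side stand.

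- **The switch is an inference.** A reader might take the plan to say that skewed outcomes are moved to rank tests. The text has no such explicit rule; it is the natural reading of a faulty sentence.
- **The mixed model covers the repeated scale scores.** It has no normality gate. It does not clearly cover the rest: healing duration and total cost are one value per patient, and the economic outcome is assessed once. The wound treatment table is completed every two weeks, so cost and time entries could in principle be modelled as repeated records. But the stated model concerns change over time on an odds-ratio scale, not total cost.
- **The sample size is not in conflict with tests on cost or waiting time.** A reader might infer that it is, but the calculation uses healing time only, and there the loss of power is slight.
- **The ICER is not made wrong.** Nothing routes it through the rank test.
- **The pre-test as such is not the cause of the excess.** Used alone, the rank test rejects more often than the two-stage rule.
- **The large figures need unequal spread.** With CV 0.5 vs 0.6 the two-stage rule is near nominal, at 5.6%.

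**Conclusion.** The point holds in a limited form. For cost, transport and waiting time totalled per patient, and healing duration, the only clearly stated between-group comparison is one whose test, and so whose target, seems to be chosen by a normality check of unstated version and threshold. For cost, this allows a p-value on rank order beside an ICER built on means.

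Under assumed lognormal costs with equal means, the disagreement ranges from none (identical distributions) to about a third of trials (CV 0.5 vs 1.0, 50 per arm), and more with the Lilliefors version. The skew and the unequal spread are assumptions. So is the use of mean costs in the ICER: this is how such a ratio is normally formed, but the article does not say how costs are averaged.

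The consequence is a possible inconsistency in reporting. It invalidates neither the ICER nor N. It is worth correcting because the remedy is cheap.

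**What to change.** 1. Remove the normality test as the selector of the between-group test, and rewrite the sentence that applies nonparametric tests to normal variables.
2. Compare total cost, transport time and waiting time by arithmetic mean difference with a bootstrap 95% CI, whatever the distribution. The cost comparison and the ICER then share one numerator.
3. Name one method in advance for healing time.
4. Rely on the planned mixed model for the repeated scale scores.
5. Keep rank tests as labelled sensitivity analyses.

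The cost is wording and a little analysis work, with no new data and no change to the 100 participants. The downside is that mean-based intervals can be wider when costs are very skewed.
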